### Study procedure

This study will generate evidence about a specific, easily implementable intervention using little resources to promote mobility and evaluate its impact on significant clinical outcomes of GIM inpatients (figure 1). Study recruitment started on 13 September 2021. Study completion is expected by 15 December 2022.

**Figure 1 F1:**
[figure not shown]
Study flowchart. DEMMI, de Morton Mobility Index; EHR, electronic health record; R, randomisation.

#### Prescreening and recruitment

All patients hospitalised on the GIM department will be prescreened during weekdays within the first 2 days of hospitalisation for study participation.

#### Baseline assessment

Study personnel will obtain written informed consent (online supplemental file 1) by the participant. After study inclusion, each patient receives a structured systematic assessment by the study coordinator including (table 2):

10.1136/bmjopen-2021-058509.supp1Supplementary data

Sociodemographic and anthropometric data (eg, age, gender, weight and height, zip code (rural versus urban living area), marital status, nurse visit at home (German: Spitex), insurance coverage (private or not), admission mode (elective or urgent), transfer from intensive care unit, hospitalisation in the last 6 months), previous use of mobility aids.Comorbidities will be reported by the participant, using an established, systematic method as previously described.^38^Functional status using Barthel index. The Barthel index is one of the most widely used and reliable functional outcome measures and is measured through an established and validated questionnaire where higher scores on a scale between 0 and 100 indicate greater independence in activities of daily living.^30^ It can be conducted by telephone and a validated German version is available.^31^ If the patient is not able to answer the questions, the Barthel index will be administered by interviewing the ward nurse caring for the patient, a family member or any other person caring for the patient before hospitalisation (eg, home care nurse).Concerns of falling using FES-I. FES-I is a validated 16-item tool to evaluate concerns of falling, with 16 score points indicating no concerns of falling and 64 score points indicating high levels of concern.^32^ It can be conducted by telephone and a validated German version is available.^33^Quality of life will be assessed with the EQ-5D-5L questionnaire. The EQ-5D-5L^34 35^ is an established, standardised measure of quality of life consisting of a descriptive system compromising the five dimensions mobility, self-care, usual activities, pain/discomfort and anxiety/depression with five levels each (no problems, slight problems, moderate problems, severe problems, and extreme problems) and a visual analogue scale with 0 indicating the worst health and 100 indicating the best health.^39^ It can be conducted by telephone interview and a validated German version is available.^36^Physical activity will be assessed by a trained study nurse using the DEMMI score. The German version of the DEMMI is a valid^40^ and reliable^39^ instrument to measure physical activity in older adults in the acute hospital setting and has no floor or ceiling effect.^28 37 41^ Based on 15 items (0–19 points with Rasch conversion to a score ranging from 0 (indicating poor physical activity) to 100 (indicating a high level of independent physical activity)), the DEMMI includes evaluation of movement in bed (three items), chair (three), static balance (four), walking (two) and dynamic balance (three). Acute older adult patients with a DEMMI score below 41 score points had significantly lower Barthel index (38% vs 79%), used more mobility aids, were more bedridden, longer hospitalised and were more often discharged to rehabilitation compared with those with a higher DEMMI score.^42^ No association was found for gender, age, weight, body mass index, Charlson comorbidity index or handgrip strength.^42^ Trained personnel is able to complete the DEMMI in no more than 10 min.

**Table 2 T2:** Summary of study procedures based on SPIRIT schedule

	First visit	Second visit*	Third visit	Phone call
Time points (days after randomisation)	0	5	At discharge†	90
Oral and written patient information	+			
Written consent	+			
Inclusion/exclusion criteria	+			
Physical activity (de Morton Mobility Index)	+	+	+	
Randomisation	+			
Demographics	+			
Installation of accelerometer	+			
Read-out of accelerometer			+	
Number of in-hospital falls			+ / daily	
Delirium episodes (EHR)			+	
Length of stay (EHR)			+	
Medical history (EHR)			+	
Destination (EHR)			+	+
Concerns of falling (FES-I)	+			+
Independence during activities of daily living (Barthel-Index)	+			+
Quality of life (EQ-5D)	+			+
Number of falls (with/without injuries)				+
Number of rehospitalisations				+
Mortality				+

*Omitted if third visit before day 6.

†Latest on day 14.

EHR, electronic health record; FES-I, Falls Efficacy Scale-International; SPIRIT, Standard Protocol Items: Recommendations for Interventional Trials.

#### Mobility measurements

To objectively measure mobilisation, patients will be equipped with a wrist-worn tri-axis accelerometer (GENEActiv, Activinsights, Kimbolton, Cambridgeshire, UK). This accelerometer has been validated and proven to reliably measure physical activity in hospitalised patients.^43 44^ At inclusion, a study nurse will instruct the patients to wear the accelerometer as long as possible during hospitalisation (day and night time) on either wrist side. The accelerometers will be collected before discharge or transfer to another hospital unit. The measurement frequency will be 50 Hz. Accelerometer data will be extracted and analysed using the GGIR package for R.^45^ Time mobilised (total minutes per day) will be calculated from time ‘moving’ as total of time ‘inactive’ and ‘static’, excluding time ‘not worn’. Mean acceleration in miliG/vector will be indicated.

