## Introduction

Decreased mobility during hospitalisation is associated with muscle loss, risk of falls, delirium, functional decline and an increased mortality, especially in the elderly.^1–4^ Bedrest of 10 days in healthy elderly resulted in a substantial loss of muscle strength, power, aerobic capacity and a reduction in physical activity.^5^ Evidence suggests that interventions that promote early mobility have the potential to decrease the risk of falls,^6 7^ to reduce functional decline during hospitalisation,^8^ to shorten duration of delirium^9^ and to reduce the median length of hospital stay (LOS) and mortality.^9 10^ Therefore, early mobilisation is recommended in most patients to prevent functional decline and frailty.^11 12^ Despite recommendations to mobilise patients early, a low level of physical activity is still common and many patients spend most of the time in bed during hospitalisation, irrespective of patient age.^3 12–14^ In a recent Dutch study, inpatients spent almost half of the time in bed and were active only 10% of the time.^15^ Most studies assessing interventions on mobilisation focused on selected patients such as older adults or those admitted to intensive care units. Further, most studies failed to monitor mobility or long-term functional outcomes or had a retrospective design.^2 12 16–18^

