Key secondary outcome	Change in DEMMI score between baseline and discharge. Mobilisation time measured by accelerometer between inclusion and day 5. Mobilisation time between inclusion and discharge. Number of delirium episodes. Number of in-hospital falls. Length of hospital stay. Total number of falls (with/without injuries) within 3 months. Number of rehospitalisations and all-cause mortality within 3 months. Independence during activities of daily living: change in Barthel index between study inclusion and 3 months. Change in FES-I between baseline and 3 months. Quality of life: change in EuroQol (EQ-5D-5L) between study inclusion and 3 months. Destination at 3 months after study inclusion (may include: death, acute care hospital, rehabilitation, home, nursing home, others).

DEMMI, de Morton Mobility Index; FES-I, Falls Efficacy Scale-International.

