### Estimated sample size and power

The sample size calculation was based on the primary outcome of a clinically meaningful change in the DEMMI score between baseline and 5 days of follow-up. The DEMMI score ranges from 0 to 100 points with 0 indicating no physical activity and 100 indicating maximal physical activity. Based on previous studies on changes in DEMMI scores during short-term hospitalisation of roughly 10 days,^26 27^ we expect a difference in change between the two groups of 5 score points. In an observational study of participants with low and high activity, SD for changes in the DEMMI score was 7.8 and 8.5 points, respectively (personal communication).^26^ In a study on older adult inpatients, the SD was between 12.5 and 15.4 points for absolute DEMMI scores at admission and discharge, respectively.^27^ The SD for changes is typically smaller than for absolute values; we therefore expect a rather conservative SD of about 10 points for the change in our study.

To detect a difference in change of 5 score points with a SD of 10 points, at a two-sided alpha level of 0.05 with a power of 0.8, a sample size of 2×64 participants is required. Based on an estimated drop-out rate of 20%, we aim to include 160 patients into the study (80 in each group).

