### Secondary outcome

Change in DEMMI score between baseline at study inclusion and discharge. Patients hospitalised for more than 2 weeks on GIM wards will be assessed on day 14 after study inclusion instead of at hospital discharge.Percentage of time moving between study inclusion and day 5. Activity will be measured using an accelerometer (GENEActiv, Activinsights, Kimbolton, Cambridgeshire, UK) validated to assess activity in the hospital setting.^13 14 29^Percentage of mobilisation time between baseline and discharge or at 14 days (whichever occurs first).Number of in-hospital delirium episodes (follow-up max. 14 days).Number of in-hospital falls (follow-up max. 14 days)LOS defined as days between hospital admission and discharge.Total number of falls (with/without injuries) within 3 months after study inclusion.Number of rehospitalisations and all-cause mortality within 3 months after study inclusion.Change in independence during activities of daily living (Barthel index) between baseline and 3 months after study inclusion.^30 31^Change in Falls Efficacy Scale-International (FES-I) between baseline and 3 months after study inclusion.^32 33^Change in quality of life (EQ-5D-5L) (visual analogue scale (EQ-VAS) and mobility dimension) between baseline and 3 months after study inclusion.^34–36^Discharge destination (death, acute care hospital, rehabilitation, home, nursing home).Reaching the minimal clinically important difference (MCID) of a change in DEMMI score (9 points) between baseline and discharge.^28 37^

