#### Statistical analysis

The statistical analysis will be performed by CTU Bern, University of Bern, using the statistical software packages Stata or R. All recorded and derived variables will be presented using descriptive summary tables. Continuous variables will be summarised by mean and SD or median and lQR as appropriate. Categorical variables will be summarised with absolute and relative frequencies.

Primary analysis will be intention-to-treat. The primary outcome change in DEMMI score from randomisation to day 5 will be compared between both intervention groups using a linear model. The model will be adjusted for the baseline DEMMI score and stratification factors used for randomisation.

Secondary continuous outcomes will be analysed using the same approach as described above. To assess change in quality of life, we will analyse the difference between baseline and day 5 or day 14 in the visual analogue scale and the mobility dimension of the EQ-5D-5L. Count outcomes (number of falls and rehospitalisations) will be assessed using a negative binomial model, categorical outcomes (destination) using a multinomial logistic model, binary outcomes (reaching MCID) using logistic regression and time-to-event outcomes (LOS, mortality) using a Cox regression model. All models will be adjusted for stratification factors. In a per-protocol analysis, patients that violated any eligibility criteria did not receive the allocated intervention or were discharged before day 4 will be disregarded.

All effect measures will be accompanied by 95% Cl. The statistical testing will be two-sided with a type I error of 5%. The data analysts will be blinded to the group.

We will perform subgroup analysis for age groups <65 years vs ≥65 years, initial performance in physical activity (DEMMI≤40 vs DEMMI>40), and prehospital mobility (no mobility aid vs prehospital use of mobility aid) because previous studies showed that older age categories had significantly lower mean DEMMI scores,^46^ and lower Barthel index and use of mobility aids or being bedridden was associated with lower DEMMI scores.^42^

Any deviation from the original statistical plan will be described and justified in the final trial report. There is no interim analysis planned, that is, there are no stopping rules on the individual or trial level.

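### The printed derivation of accelerometer mobilisation time contradicts itself and the outcome list in content and scale, and applied literally could reverse two secondary outcomes

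*Protocol article*

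**What the plan says.** Three places in the protocol article describe the accelerometer outcomes.

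- **Table 1, key secondary outcomes:** "Mobilisation time measured by accelerometer between inclusion and day 5", with a second entry running to discharge. No unit is given.
- **Secondary outcome:** "Percentage of time moving between study inclusion and day 5" and "Percentage of mobilisation time between baseline and discharge or at 14 days (whichever occurs first". Both are percentages.
- **Mobility measurements:** the purpose is stated as "To objectively measure mobilisation, patients will be equipped with a wrist-worn tri-axis accelerometer", and the derivation is "Time mobilised (total minutes per day) will be calculated from time ‘moving’ as total of time ‘inactive’ and ‘static’, excluding time ‘not worn". The unit is minutes per day.

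The classes 'moving', 'inactive' and 'static' are not defined anywhere in the article. The Mobility measurements section adds that mean acceleration will also be reported. For the comparison between arms, the Statistical analysis section says "Secondary continuous outcomes will be analysed using the same approach as described above", which means a linear model.

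**The concern.** The article did not leave the derivation to another document. It printed one, and it is the only one given for these two outcomes. In ordinary usage 'inactive' and 'static' are the classes in which a patient is not moving. Their total is the complement of the quantity that the outcome list names.

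The scale is a separate conflict. Leaving non-wear out of a minutes total does not standardise that total, because a patient who wears the device for fewer hours can only accumulate fewer minutes. Patients are asked to wear it for as long as they can, so wear will vary.

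The accelerometer is listed among the study's strengths as the record of the intervention's effect, and adherence is otherwise judged only by whether the goal board is present at discharge. If the derivation were programmed as printed, a patient who moved more would get a lower value, and a benefit on these two outcomes could be reported as harm. If minutes were used, activity and wear time would be mixed.

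**Working it through.** **Plan's own figures.** The article gives no expected value, SD or power for the accelerometer outcomes, so there is nothing to reproduce for them. Its sample size concerns the DEMMI (difference 5, SD 10, two-sided alpha 0.05, power 0.8). The t-test calculation gives 63.77, rounded up to 64 per arm, and 64 / 0.8 = 80 per arm, or 160 in total. This matches the article, and nothing below changes it.

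**Inputs for the illustration**

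- Moving share in the control arm: 10%. This is an assumption, borrowed from a cited study in the Introduction in which "inpatients spent almost half of the time in bed and were active only 10% of the time". It is not a design input of this trial.
- Moving share in the intervention arm: 12.5%. This is an assumption, chosen only to show direction.
- Wear: 1440 minutes per day in both arms (assumption).
- The three classes are exclusive and together make up worn time (assumption, since the article does not define them).

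Minutes moving are 0.10 × 1440 = 144 (control) and 0.125 × 1440 = 180 (intervention). Inactive plus static is 1440 − 144 = 1296 and 1440 − 180 = 1260.

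**Three readings of the sentence**

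| Reading | Control | Intervention | Difference |
|---|---|---|---|
| (a) Mobilised = inactive + static, as % of worn time | 1296/1440 = 90.0% | 1260/1440 = 87.5% | −2.5 points (−36 min) |
| (b) Moving as % of inactive + static | 144/1296 = 11.1% | 180/1260 = 14.3% | +3.2 points |
| (c) Moving = worn time less inactive and static, as % of worn time | 144/1440 = 10.0% | 180/1440 = 12.5% | +2.5 points (+36 min) |

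Only (a) reverses the sign. Reading (b) has the right direction but an odds-like scale. Reading (c) is the quantity in the outcome list.

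**Dependence on the assumed 10%.** On the percentage scale, reading (a) equals 100 minus the moving percentage. Moving shares of 5%, 10% and 20% would be recorded as 95%, 90% and 80%. A true difference of d points becomes −d whatever the starting share.

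**Dependence on wear.** At 10% moving, 24 hours of wear gives 144 minutes and 12 hours gives 0.10 × 720 = 72 minutes, half the value at the same activity.

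Now let control wear be 1200 minutes with 144 moving, and intervention wear 1440 minutes with 180 moving (both assumed):

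- Inactive + static in minutes: 1200 − 144 = 1056 against 1440 − 180 = 1260, a difference of +204.
- Moving in minutes: 180 − 144 = +36.
- Moving as % of worn time: 144/1200 = 12.0% against 180/1440 = 12.5%, or +0.5 points.
- Inactive + static as % of worn time: 88.0% against 87.5%, or −0.5 points.

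The reversal is therefore exact for percentages of worn time, or for minutes with equal wear. For minutes with unequal wear, the literal reading gives a wear-time artefact that need not have the reversed sign.

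**The case against.** The strongest reply is that this is a drafting slip. The sentence itself names 'moving' as the source, the outcome list speaks of time moving, and the section opens by saying that the device is there to measure mobilisation. An analyst would have to set all three aside to programme the reversal. Dropped words, such as a phrase making 'moving' a share of the total, are at least as likely. That is fair. A reader might infer that both outcomes will be computed with the sign reversed, and the documents do not support that: reversal is one of several readings.

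A reader might also infer that these are the trial's only objective evidence on activity. They are not. Mean acceleration from the same device is also to be reported and does not depend on the disputed classes, and the DEMMI is a performance test scored by a blinded physiotherapist. A mobilised share near 90%, or a conflict with mean acceleration, might well alert someone.

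On scale, the percentages in the outcome list together with the exclusion of non-wear point towards worn time as the denominator. The wear-time problem arises only if the minutes in the derivation are what is analysed. A reader might further infer that wear will differ between arms because the trial is open-label, but the article gives no wear data, so that is conjecture.

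Finally, the article refers to a prespecified analysis plan that is not shown and may define the classes. That weakens any prediction of what will be programmed. It does not make the printed derivation right, and nothing in the article says which of the conflicting statements governs.

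**Conclusion.** The point holds as an internal contradiction. The only printed derivation of mobilised time conflicts with its own source word and with the outcome list, and its unit conflicts with the unit of the outcomes. Two of the thirteen listed secondary outcomes are affected.

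Applied literally, the derivation could reverse their direction: 144 minutes moving would be recorded as 1296 minutes (90%) mobilised. That figure rests on an assumed 10% moving share, full wear, and classes that are exclusive and exhaust worn time. The sign reversal on the percentage scale needs only the last of these assumptions. The contradiction itself needs none of them.

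**What to change.** Replace the derivation sentence with a definition along these lines: mobilisation time (%) = 100 × 'moving' / ('moving' + 'inactive' + 'static'), with 'not worn' time excluded from numerator and denominator, calculated over each window (inclusion to day 5; inclusion to discharge or day 14, whichever is earlier). Say briefly what each class means. Use the same name and scale in Table 1, the Secondary outcome section and Mobility measurements. If minutes per worn day are wanted, report them as description only.

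Check the derivation code against this definition before unblinding. The cost is one rewritten sentence, two aligned outcome entries in Table 1 and the outcome list, and a code check. No new data are required.

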#### Randomisation and allocation procedures

After patient registration in the data entry system (REDCap) and confirmation of all inclusion and exclusion criteria, patients are randomised 1:1 to one of the two study groups. Randomisation will be blocked using varying block sizes of 2, 4 and 6. Moreover, randomisation will be stratified according to the baseline DEMMI score (≤40 vs >40 points) and age (<65 vs ≥65 years). The allocation sequence (randomisation list) will be generated by an independent data manager at CTU Bern, University of Bern, Bern, Switzerland not otherwise involved in the trial and implemented in the data entry system to ensure concealment of allocation.

#### Statistical analysis

The statistical analysis will be performed by CTU Bern, University of Bern, using the statistical software packages Stata or R. All recorded and derived variables will be presented using descriptive summary tables. Continuous variables will be summarised by mean and SD or median and lQR as appropriate. Categorical variables will be summarised with absolute and relative frequencies.

Primary analysis will be intention-to-treat. The primary outcome change in DEMMI score from randomisation to day 5 will be compared between both intervention groups using a linear model. The model will be adjusted for the baseline DEMMI score and stratification factors used for randomisation.

Secondary continuous outcomes will be analysed using the same approach as described above. To assess change in quality of life, we will analyse the difference between baseline and day 5 or day 14 in the visual analogue scale and the mobility dimension of the EQ-5D-5L. Count outcomes (number of falls and rehospitalisations) will be assessed using a negative binomial model, categorical outcomes (destination) using a multinomial logistic model, binary outcomes (reaching MCID) using logistic regression and time-to-event outcomes (LOS, mortality) using a Cox regression model. All models will be adjusted for stratification factors. In a per-protocol analysis, patients that violated any eligibility criteria did not receive the allocated intervention or were discharged before day 4 will be disregarded.

All effect measures will be accompanied by 95% Cl. The statistical testing will be two-sided with a type I error of 5%. The data analysts will be blinded to the group.

We will perform subgroup analysis for age groups <65 years vs ≥65 years, initial performance in physical activity (DEMMI≤40 vs DEMMI>40), and prehospital mobility (no mobility aid vs prehospital use of mobility aid) because previous studies showed that older age categories had significantly lower mean DEMMI scores,^46^ and lower Barthel index and use of mobility aids or being bedridden was associated with lower DEMMI scores.^42^

Any deviation from the original statistical plan will be described and justified in the final trial report. There is no interim analysis planned, that is, there are no stopping rules on the individual or trial level.

